## Abstract

**Background:**

Edible insects are a sustainable source of high-quality animal protein. Insect farming is gaining interest globally, particularly in low-income countries, where it may provide substantial nutritional and economic benefits. To enhance insect farming practices in Africa, new farming systems are being developed. However, knowledge on how to best promote uptake of these systems is lacking. This study aims to fill this gap by investigating the effectiveness of educational interventions in promoting insect farming for household consumption in Africa.

**Method:**

The study is designed as a multi-site randomized controlled trial to evaluate the impacts of agricultural training alone or in combination with nutrition education on the adoption of insect farming in Ghana, Kenya and Uganda. In each of the three countries, ninety-nine villages are randomly assigned to one of three arms: two intervention arms and a control arm with no interventions. Focusing on production (P), the first intervention arm covers agricultural training on insect farming combined with provision of insect production starter kits. Focusing on both production and consumption (PC), the second intervention arm involves the same intervention components as treatment P plus additional nutrition education. The impacts of the interventions are measured by comparing baseline and endline data collected one year apart. Primary outcomes are adoption of insect farming and consumption of the farmed insects.

**Discussion:**

Understanding the drivers and impacts of novel agricultural practices is crucial for transitioning to sustainable food systems. The current project is the first to investigate how educational interventions promote insect farming for household consumption in low-income countries. The results will contribute evidence-based knowledge to support sustainable development through insect farming in Africa.

**Trial registration:**

The protocol is registered in the American Economic Association registry for randomized control trials with registration number AEARCTR-0009996. Initial registration date: 02 September 2022, last updated 17 May 2023.

## Introduction

The vast majority of agricultural production in Sub-Saharan Africa is dependent on rain, making it highly vulnerable to the effects of climate change such as increasing frequency and severity of droughts [1]. This is expected to increase food insecurity and malnutrition [2]. At the same time, rapid population growth in Africa is driving an increasing demand for nutritious and healthy foods. Satisfying this demand in the face of climate change calls for a transition towards more sustainable and resilient agricultural practices [3], which is key to safeguarding livelihoods and improving food security and nutrition in the long term [4–7]. For smallholders, this transition involves finding and employing alternative low-cost farming approaches that have minimal land, water and feed requirements [3, 5, 6].

Farming edible insects is an alternative livestock production system with multiple potential benefits [5, 8, 9]. First, insect farming can assist nutrition improvement activities in food-insecure areas, as insects are generally rich in high-quality animal protein and essential micronutrients [10]. Second, compared to other livestock production, insect farming is characterized by lower greenhouse gas emissions. Additionally, it holds the potential to produce food that is nutritionally equivalent to livestock while requiring less water, land, and other inputs. These potentials make insect farming resilient to the anticipated effects of climate change [11, 12], positioning it as a climate-smart agricultural practice [13]. Third, insect farming may support rural livelihoods in Africa by creating employment opportunities and generating cash income for households [14]. Despite these potential benefits, insects have mainly been harvested in the wild and consumed seasonally or sporadically in traditional diets in many parts of the world [15]. This practice of wild harvesting has led to overexploitation of insect specifies, and the consumption of insects in traditional diets is declining globally, largely due to the influence of westernized eating habits [16–18]. To address these challenges, insect farming has emerged as a viable solution to promote insect consumption through sustainable production systems [5, 16]. Furthermore, the growing emphasis within the agricultural sector to meet the increasing demand for nutritious and environmentally sustainable foods has highlighted the potential of insect farming as a novel approach to animal-based food production globally [4, 5, 8].

Compared to other agricultural production sectors, insect farming is relatively young and most producers operate on a limited scale [14, 19]. Legislative barriers often impede growth of this sector [20]. However, some progress has been made in improving legislative frameworks, especially in Africa [9]. For instance, in Kenya and Uganda, insects are recognized as indigenous foods, and standards have been developed for their regulation [21, 22]. The development and promotion of insect farming has so far had limited anchorage in research and innovation [9]. However, stakeholders in private and public sectors are currently focusing on innovation and knowledge transfer activities to develop farming systems including rearing facilities and management practices suitable to various insect species [9, 23, 24]. This has led to the emergence of several new insect farming systems around the world [5, 9, 14]. For instance, cricket farming has been developed and successfully implemented in Thailand [24, 25]. Similar farming systems are currently being adopted and promoted in Africa to produce insects on small, medium and large scales [5, 9, 26]. A recent country-level rapid survey conducted by the World Bank reveals that insect farming is practiced in 10 out of the 13 surveyed countries in Africa [5].

Several studies have explored various aspects of utilizing insects as human food, and their findings have been compiled in review studies. These studies suggest that consumers in developing countries generally exhibit positive attitudes towards insects as a food source. Additionally, the studies emphasize that insects are a valuable and safe source of essential nutrients, which can be produced with minimal negative environmental impacts [10, 18, 27]. However, little is known about the most effective approaches to promote insect farming, especially in an African context. If the aim is to promote insect farming to support livelihoods and food provision in rural Africa, targeted interventions need to be identified and tested for their effectiveness. The current study conducts a randomized control trial (RCT) in three Sub-Saharan Africa (SSA) countries, namely Ghana, Kenya and Uganda, to investigate the effectiveness of educational interventions in promoting small-scale insect farming and household consumption. The focus on educational interventions was informed by previous studies indicating that lack of knowledge and skills in relation to both insect farming practices and nutritional benefits of consuming insects are the main causes of low uptake of insect farming for household consumption [21, 28]. By providing new, evidence-based knowledge on the promotion of small-scale insect farming and consumption in SSA, the study contributes to the advancement of appropriate policies for realizing the full potential of insect farming for sustainable development. Specifically, the study addresses several of the UN’s Sustainable Development Goals, including improving livelihoods (SDG1), improving nutrition and health (SDG2), supporting gender equality (SDG5), creating job opportunities (SDG8), reducing environmental impacts (SDG13), and promoting partnerships to achieve the different goals (SDG17) [5, 7].

## Methods and materials

### Study setting

The selection of Ghana, Kenya and Uganda for our study is justified as follows. First, consumption of insects collected from the wild is a part of local food cultures in all the three countries, providing nutritional and economic benefits to the population [29]. People in these countries are thus not completely new to the notion of eating insects. In addition, insect farming activities are emerging in the three countries driving innovation and sustainable development [5, 9]. Second, the multisite intervention study across an east-west gradient enables coverage of a variety of cultural contexts and agro-climatic conditions in SSA, enhancing the external validity and generalizability of our findings to other parts of SSA. Third, findings generated from this study can provide inputs for stakeholders involved in developing legislative and regulatory frameworks for the use of insect as food in the three countries. Thus, the multisite approach can strengthen the institutional frameworks needed to establish sustainable edible insect value chains and food systems in Africa. Fourth, our study involves three different insect species across the three countries, selected based on their likelihood of acceptability within the local culture and the availability of insect farming systems tailored to their specific life cycle and needs [23]. These species include Palm weevil larvae (*Rhynchophorus phoenicis*) in Ghana, Crickets (*Scapsipedus icipe*, *Acheta domesticus)* in Kenya, and African edible bush crickets (*Ruspolia differens Serville*) in Uganda [26, 30, 31]. The inclusion of diverse farming systems allows us to comprehensively analyze approaches to promote the adoption of farming practices and consumption of culturally appropriate insect species on a broader scale. The study thus contributes to the development of a generic framework for describing impact pathways of small-scale insect farming in relation to improving nutrition, health and livelihoods.

### Study design

The study involves a 1:1 cluster-RCT with two intervention arms. The first intervention arm focuses on insect production. It includes agricultural training on insect farming and the provision of insect production starter kits *(Treatment P)*. The second intervention arm is focused on insect production plus insect-based food consumption. It has the same intervention components as *Treatment P* plus an additional component focused on nutrition education and insect cooking demonstrations *(Treatment PC)*. A control arm with no interventions *(Control)* serves as a comparison group for the treatments. The effectiveness of the interventions is evaluated by comparing baseline and endline data collected one year apart.

### Program theory

Based on the literature identifying the complex pathways linking agricultural interventions and health and nutrition outcomes [32, 33], we develop a conceptual framework for the study as shown in Fig 1. The conceptual framework presents the problems, the resources and activities to tackle the problems, and the resulting impacts. The agricultural training components are expected to address the lack of knowledge about insect farming in rural communities and affects the drivers associated with knowledge, perceived benefits and risks, technology access, and willingness to adopt insect farming. The nutrition education and cooking demonstration interventions are expected to address the lack of knowledge and awareness about the benefits of insect consumption and the lack of insect-based food preparation skills. The interventions affects all the drivers in Fig 1 except for technology access. The short-term impacts of the intervention activities are likely to be improved knowledge of insect farming and cooking insect-based foods, and the benefits of insect consumption, positive perception of insect farming and consumption, decreased likelihood of experiencing food insecurity, and increased willingness to adopt. These short-term impacts can lead to medium-term impacts consisting of increased insect consumption, increased dietary diversity, insect production, and income generation. The combined short- and medium-term impacts can result in long-term impacts, which are part of the UN Sustainable Development Goals.

**Fig 1 pone.0288870.g001:**
[figure not shown]
Conceptual framework showing pathways between the interventions and their outcomes.

### Study aims and objectives

The overall aim of the project is to generate evidence regarding the effectiveness of educational interventions in promoting insect farming for household consumption in Africa. More specifically, the main objectives are:

To evaluate the impacts of insect farming and nutrition education interventions on household adoption of insect farming and consumption of farmed insects.To develop an evidence-based framework describing impact pathways from promoting insect farming and consumption to outcomes related to insect production and consumption, with a particular focus on potential long-term development outcomes related to nutrition, health, and livelihoods.

### Sample size

To calculate the sample size, we determine the minimum detectable effect size based on the best available data in the literature regarding the effects of educational programs on adoption of insect farming. In Ghana, Kenya and Uganda, insect farming remains relatively uncommon compared to other types of farming activities. For instance, in a pilot study on cricket (*Scapsipedus icipe*, *Acheta domesticus)* farming in Kenya, only 12% of the sampled farmers adopted cricket farming [28]. We use this information to determine the minimum detectable effect size in our power analysis. We assume a minimum detectable effect size of 0.25 for Kenya, as an effect size of 0.12 would be too small to be detected given the available budget for the study. In Ghana, 560 farmers were trained as part of a pilot project focusing on farming Palm Weevil (*Rhynchophorus phoenicis*) production near their homes or gardens [34]. The same study reported that 48% of the trained farmers were actively farming Palm Weevil after the training. To avoid overestimation of the effect size, we consider a minimum detectable effect size of 0.25 for Ghana. In Uganda, pilot studies indicating the proportion of farmers involved in the farming of African bush crickets (*Ruspolia differens Serville*) were not found. Thus, we refer to related studies on the adoption of climate-smart agriculture practices in Uganda. Accordingly, we assume a minimum detectable effect size of 0.25 based on a previous study concerning climate-smart agricultural interventions [35].

Using the Optimal Design Software for multilevel and longitudinal research [36], the sample size is calculated based on a 0.8 power, 0.05 significance level and 0.06 intra-cluster correlation coefficient. Fig 2 shows that a total of 64 clusters (villages), each with 15 participants, are needed to obtain 80% of power for cluster randomized designs with two intervention groups. The minimum sample size across each of the intervention and control arms thus includes 32 villages in each country. To ensure that we detect the same effect size or smaller, we increase the sample size to 33 villages for each of the intervention and control arms.

**Fig 2 pone.0288870.g002:**
[figure not shown]
Power versus number of clusters.

Based on our experience from previous farming and nutrition intervention studies in the three countries, we expect an attrition rate of no more than 10%. Thus, the number of participants is increased by 10% to accommodate for attrition in our sample size calculation. To reduce the attrition rate, the implementation team visits the participants frequently to address any concerns related to the intervention. The implementation team also arrange alternative meeting schedules in case the participant is unavailable during endline surveys. Any missing values resulting from attrition are dropped from data analysis.

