Study arm	Clusters	Baseline survey	Intervention with participant endline survey			Community endline survey
	Villages	Participants^a^ per village	Participants per village	Participants per arm	Participants per arm (extra 10% added)^b^	Participants per village^c^
Treatment *P*	33	30	15	495	545	15
Treatment *PC*	33	30	15	495	545	15
Control	33	30	0	0	0	30

Note: ^a^ Participants are household represented by the head of the household.

^b^ The number of participants per treatment arm was increased by 10% to account for attrition.

^c^ The remaining 15 participants per village from the baseline survey who are not part of the intervention are included in the community endline survey. No interventions are implemented in the control villages, therefore, all the 30 household are included in this survey.

To ensure research integrity and methodological rigor, the village randomization process is blinded to all individuals involved in the research and households residing in the 99 villages prior to the intervention. A randomized sequence is generated in STATA [41] by a colleague not involved in the research. The outcome of the randomization is only revealed to project staff and households after the randomization process is completed. During the intervention, blinding is not maintained, except in the control villages where households are unaware of the intervention. Project staff members only visit control villages during the baseline and endline surveys, and no visits are conducted during the intervention to prevent information leakage and reduce potential biases that could arise from knowledge of the intervention in the control group.

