The training activities begin with inviting the selected household heads to an information meeting. Here, participants are briefed on the purpose and nature of the intervention, what they can expect during the intervention, and what they are expected to do as participants. At this point, participants are made formally part of the intervention and assigned an identification number. Implementation teams are formed and receive training before commencing the interventions. They are responsible for providing the agricultural training according to the training manual. An implementation team consists of two persons assigned to half of the villages in each treatment arm and conducts the training on a rotating basis to avoid bias induced by the implementation team.

For example, if *Implementation Team 1* covers the first half of the villages in *Treatment P*, *Implementation Team 2* covers the first half in *Treatment PC*. Then, the team rotates, where *Implementation Team 1* covers the other half of the villages in *Treatment PC* while *Implementation Team 2* covers the other half in *Treatment P*. The training is given in a rolling sequence, i.e., the implementation team conducts training in one village at a time and continues until all villages are covered. The same implementation team visits each participant at least once a month to reinforce training messages and provide technical support for insect farming activities. These visits are important for participants as they give opportunities to raise questions and for the implementation team to tailor messages according to the specific contexts of the participant [43].

*Distribution of production starter kits for insect farming*. After the agricultural training, each participating household head receives a starter kit for free for small-scale insect farming. While the specific composition differs across the three countries due to differences in the types of insects selected for farming, the starter kits generally consist of live insects or eggs, insect rearing equipment and container, feed for insects, and a cleaning kit (see Table 3).

**Table 3 pone.0288870.t003:** Starter kits by country and insect species.

Country	Type of insect to be farmed	Main components of starter kits

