### Outcomes

#### Overview of outcome variables and measurements

*Primary outcomes variables*. The primary outcome variables indicating the impacts of the interventions are: 1) whether farmed insects are consumed in the household, and 2) adoption of insect farming. The first primary outcome variable is measured during the baseline and endline surveys using questionnaires that inquire whether the participants cook and consume farmed insects. For participants, who cook and consume the farmed insects, they are asked to indicate the frequency of consumption within the last one year using a five-point scale ranging from 1–3 times per month to 1 or more times per day. The second outcome variable is measured through direct observation to determine whether the participant is still engaged in insect farming at the time the endline survey is conducted. Engaging in insect farming activities entails management of an insect farm, as well as harvesting and postharvest practices, as described in Table 2.

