
### Data collection

Data is collected through two rounds of household surveys in each village on a rolling basis. As shown in Fig 3, the baseline survey is conducted in each village before villages are randomly assigned to the intervention and the control groups. Second, the endline survey is conducted after the end of the interventions to measure intervention impacts, which are measured using selected outcome variables. The endline survey has two components: participant endline survey and community endline survey (Fig 3). The former is conducted with the 15 participants (household heads) who take part in the interventions (Treatment P or Treatment PC) in each village. The latter is conducted with the remaining 15 household heads who participated in the baseline surveys but were not selected to participate in the interventions. Since no intervention is implemented in the control arm, all the 30 household heads who participated in the baseline surveys are included in the community endline survey for the villages allocated to this arm. Training is given to field data collectors (*survey team*) responsible for baseline and endline surveys. They are trained on the content of questionnaires, question-asking techniques and cultural sensitivity [43]. Supervisors are responsible for quality control in the field and addressing issues arising during data collection. Data collectors involved in baseline surveys are blinded in such a way that they are instructed not to share any information in the villages regarding the randomization of the villages into the intervention or control group. This is important to ensure that their interactions and communication with the villages do not unintentionally disclose any information about the intervention that could influence its later implementation.

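### Missed endline meetings are re-scheduled by the team that delivers the intervention, and no equivalent is described for control households

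*Protocol article*

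**What the plan says.** The attrition paragraph of the Sample size section names two retention measures and gives both to the implementation team. The first is regular contact: "To reduce the attrition rate, the implementation team visits the participants frequently to address any concerns related to the intervention". The second concerns the endline itself: "The implementation team also arrange alternative meeting schedules in case the participant is unavailable during endline surveys". The same paragraph expects at most 10% attrition and removes missing values from the analysis.

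Components of Treatment P defines that team. "They are responsible for providing the agricultural training according to the training manual", and "An implementation team consists of two persons assigned to half of the villages in each treatment arm". Contact continues after training: "The same implementation team visits each participant at least once a month to reinforce training messages and provide technical support". Table 5 lists the team's monitoring work for the treatment groups only.

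The endline belongs to another team. Data collection describes a survey team "responsible for baseline and endline surveys", and Table 5 gives it the endline in both treatment and control groups. For control villages, Recruitment and randomization says: "Project staff members only visit control villages during the baseline and endline surveys". It also says that blinding is not kept up during the intervention, except that control households do not know of it.

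Under Outcomes, adoption is "measured through direct observation to determine whether the participant is still engaged in insect farming at the time the endline survey is conducted". The other primary outcome, consumption of farmed insects, is asked by questionnaire.

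**The concern.** The survey team is otherwise separate from the people whose work is being evaluated. The re-scheduling sentence breaks that separation at the point where the primary outcomes are measured. Two routes to bias follow.

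1. **Prompting.** A household that missed its endline visit hears from its own trainer before the survey team returns. Adoption rests on one observation and consumption on self-report, so a prompt at that moment could affect either. Eligible villages have had no earlier insect farming, so control adoption should be low. Any rise in the treated arms would then pass almost wholly into the comparisons with control.
2. **Unequal follow-up.** The described retention effort is at least monthly contact plus re-scheduling for treated households, and no contact between surveys for control households. Because missing values are dropped, unequal completeness goes straight into the analysed sample.

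**Working it through.** **1. The plan's own figures.** Inputs from Sample size: effect size 0.25, intra-cluster correlation 0.06, 15 per village, alpha 0.05 (taken as two-sided), power 0.80. With the cluster-randomised F-test, lambda = J × d² / (4 × (rho + (1 − rho)/m)). For J = 64 this is 64 × 0.0625 / (4 × (0.06 + 0.94/15)) = 8.15, and power on 1 and 62 degrees of freedom is 0.80. The stated 64 villages reproduce. The attrition addition also reproduces: 33 × 15 = 495, and 495 × 1.10 = 544.5, shown as 545. This point disputes neither figure.

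**2. Who does what.**

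| Task | Treated villages | Control villages | Source |
|---|---|---|---|
| Training and monthly visits | Implementation team | None | Components of Treatment P; Recruitment and randomization |
| Endline data collection | Survey team | Survey team | Data collection; Table 5 |
| Re-scheduling missed endline meetings | Implementation team | Not described | Sample size |

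The last row conflicts with the division of work in the second and differs by arm as described. Table 1 points the same way: its 10% addition for attrition is applied to the two treatment arms only (545, 545, 0).

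**3. Possible size of prompting (illustration).** Let u be the share of treated households re-booked, p true adoption, and r the share of re-booked households that had stopped farming and resume for the visit. Assume that re-booked households have the same adoption as the rest. The rise in measured adoption is u × (1 − p) × r. The factor (1 − p) is needed because a household still farming cannot be revived. The protocol gives neither u nor r. I take u = 10% and r = 10-50%. For p, I use the two pilot figures in Sample size (12% Kenya, 48% Ghana), with 25% as a middle value.

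| p | r = 10% | r = 50% | ceiling, r = 100% |
|---|---|---|---|
| 12% | 0.10 × 0.88 × 0.10 = 0.9 points | 4.4 | 8.8 |
| 25% | 0.10 × 0.75 × 0.10 = 0.75 | 3.75 | 7.5 |
| 48% | 0.10 × 0.52 × 0.10 = 0.5 | 2.6 | 5.2 |

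With u = 5% every entry halves.

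**4. Direction of attrition bias.** If 10% of a treated arm is lost and dropped, complete-case adoption is (p − 0.10 × q)/0.90, where q is adoption among the lost. At p = 25%:
- q = 0: 0.25/0.90 = 27.8%, a shift of +2.8 points.
- q = 25%: no shift.
- q = 45%: (0.25 − 0.045)/0.90 = 22.8%, a shift of −2.2 points.

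**5. Netting the two.** Suppose the hard-to-reach 10% had all stopped farming. Losing them gives +2.8 points at p = 25%. Having their trainers re-book them gives 0.10 × r, which is +1.0 point at r = 10% and +5.0 at r = 50%. Re-booking by trainers can thus be better or worse than losing these households.

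**The case against.** The strongest reply is that much of the harm is inferred.

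- **A reader might infer that control households get no re-scheduling.** The documents do not say so. Staff do visit control villages at endline, the attrition paragraph speaks of participants in general, and note a to Table 1 uses that word for baseline households in every arm. A condensed article may leave control call-backs to field manuals. This stands: the text describes no equivalent for controls, but does not deny them one.
- **A reader might infer that treated households are forewarned and adoption is inflated.** That is possible, not stated. The survey team makes the observation, only households unavailable at endline are affected, and nothing says other endline visits are unannounced. Any booked visit gives notice. Engagement as defined under Outcomes also covers harvesting and post-harvest practice, and a lapsed farm would need new live stock. All this makes revival less likely. What remains is that the notice comes from the trainer, in the treated arms.
- **A reader might multiply the share re-booked by the share reviving**, for example 0.20 × 0.50 = 10 points. That counts households still farming as revivable. The same inputs with the factor (1 − p) give 0.20 × 0.88 × 0.50 = 8.8 points at 12% adoption and 0.20 × 0.52 × 0.50 = 5.2 at 48%, and no passage supports either input.
- **Re-booking also helps**, because it recovers households that would otherwise be dropped. This stands, and it is why no net direction can be claimed. It is a reason to keep call-backs, not to leave them with the trainers.

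**Conclusion.** The concern holds as a flaw in a stated rule, not as a demonstrated bias. The article gives part of the endline process to unblinded staff who deliver the intervention and whose described work is in treated villages. This sits badly with its own assignment of the endline to the survey team in all arms. The rule can prompt treated households before measurement and can make follow-up differ between treated and control arms.

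The illustrative effect on measured adoption is about +0.5 to +4.4 points. It rests on three assumptions that the documents do not supply: 10% re-booked, 10-50% of lapsed households resuming, and re-booked households otherwise like the rest. The net direction, once attrition is counted, is not known.

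The exposed comparisons are each treatment against control. Treatment P against Treatment PC is largely protected, since both arms have implementation teams that rotate between them. The change is cheap and should be made before endline starts; Trial status says that follow-up data collection had not begun.

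**What to change.** Replace the re-scheduling sentence in the attrition paragraph of Sample size with a rule to this effect:

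- The survey team makes all endline appointments and call-backs.
- The procedure and number of attempts are the same in every arm, in all 99 villages of each country.
- Implementation staff do not contact households about endline visits.
- Contact attempts and attrition are reported by arm.

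This also brings the paragraph into line with Data collection and Table 5. There is no need to require that the farm be observed before a new appointment is fixed. Recruitment and randomization says that farming is typically indoors, so it could not properly be inspected while the household is unavailable.

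The cost is a change of wording and field instructions, some extra call-backs by the survey team, and the loss of the trainers' help in tracing households. The sample size does not change.
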